#### Qualitative

Quantitative findings will be contextualized by qualitative in-depth interviews (IDIs) with providers and women to evaluate performance of the intervention. Twelve IDIs will be conducted with providers after they have received training through the FIGO intervention to understand their experiences with the training and facilitators as well as barriers to intervention implementation in their hospital. Two providers will be recruited from each hospital and purposively selected to represent different cadres of provider, where multiple cadres are trained, or by provider’s sex. Twenty-four IDIs will be conducted with women who have had at least two antenatal care visits following the start of the intervention to explore women’s experiences with postpartum contraceptive counselling during antenatal care and decision-making regarding postpartum contraceptive use. Four women will be purposively selected from each hospital based on socio -demographic characteristics. Finally, IDIs will be conducted with an additional 36 women who received a PPIUD after intervention implementation. These IDIs will be conducted at least nine months postpartum to understand women’s experiences using the PPIUD. Six women will be purposively selected from each hospital based on whether they have continued or discontinued PPIUD over the postpartum period. Interviews will be audio-recorded with participants’ permission, transcribed verbatim in the local language, and translated to English.

### Data management and monitoring

Data will be securely transferred from the Android tablets onto a CommCare-supported secure cloud server at the end of each working day. The CommCare cloud server is HIPAA-compliant and meets all the necessary security requirements for storing Level 4 identifiable data as defined by Harvard University. Once the data have been securely transferred to the cloud server, the survey record on the Android tablet is immediately erased. All data uploaded to the CommCare cloud server is encrypted and password-protected in accordance to the Level 4 data security and storage regulations. For each collected data case, which will consist of a participant data record, all personal identifiable data will be separated from the other non-identifiable data. The de-identified data will then be uploaded to an encrypted password-protected FTP site on a daily or weekly basis and will be circulated to the project investigators for analysis purposes for the duration of the study. Internal consistency checks and data validation are built into the CommCare software, but de-identified data are also cleaned monthly to promote data quality. Identifiable data will be stored separately from the de-identified data on the CommCare secure encrypted server for the duration of the study. Identifiable data will only be accessed by in-country collaborators for the purpose of revisiting participants at the appropriate follow-up periods.

Each country will have an independent Data and Safety Monitoring Board (DSMB) to be comprised of three to five members with at least: one epidemiologist or biostatistician, one reproductive health expert, preferably an obstetrician/gynaecologist (OB/GYN), and one social scientist or ethicist. Each DSMB will meet every four months to review interim results and monitor compliance with the study protocol and review any adverse events associated with the intervention, such as higher than expected expulsion or complication rates. Additional information can be found in the Terms of Reference for the PPIUD study DSMBs, which is available upon request.

Study enumerators are responsible for filling out a Protocol Deviation/Adverse Event Report. Reports will be submitted to the interview supervisors, and reviewed by the national study coordinator and the principal investigator. Reports will also be shared with the country’s DSMB and IRB.

### Planned analyses

#### Quantitative analyses

To assess the causal effect of the intervention on the antenatal counselling for PPIUD uptake, successful PPIUD insertion, and continued use of PPIUD 9 and 18 months following delivery, individual-level conditional logistic regression models will be used, stratifying on hospital, and controlling for calendar time to remove bias due to secular changes in outcomes unrelated to the intervention, with the causal effect estimated by a binary indicator of the status (standard of care or intervention) of each woman’s hospital at the time of her delivery. Semi-non-parametric methods to model secular trends will be used to control for confounding by secular trends as finely as needed [18].

Due to the randomized stepped-wedge design, results will be reported adjusted only for hospital and calendar time, alongside full multivariable adjusted results, in which all measured known or potential determinants of these outcomes are controlled for. Risk differences and risk ratios will be reported, as transformations of the odds ratios to be estimated by the conditional logistic regression model. Causal inference will be strongest when analysis is restricted to the subset of women enrolled during months 4-9 of the project, although power will likely be insufficient to detect effects of realistic sizes.

Selective loss to follow-up could be a concern for valid estimation of the causal effect of the intervention on PPIUD utilization 9 and 18-months post-delivery of the index pregnancy, but active follow-up with home visits will minimize this potential bias. Also, to account for this, marginal structural models for dependent censoring will be applied [19, 20], weighting individual observations by the inverse of their probability not to be lost to follow-up, as a richly parameterized function of all measured potential determinants of the relevant outcome. Attrition analysis would examine whether the characteristics of women lost to follow-up are different than those completing follow-up interviews. Effect modification by country and other key features will be explored by assessing the significance of any differences observed through likelihood ratio tests in which the relevant cross-product term is in and out of the model and by reporting stratum-specific point and interval causal effect estimates for any statistically significant differences. Should no effect modification by country be evident, we shall aggregate the data from the three countries and produce a single summary effect estimate as above. Standard meta-analysis techniques will be used to assess between country differences, including the Q-test [21], I^2^ [22] and CV_*B*_ [23]. The study is not designed or powered to estimate differential effects by subgroups of providers, facilities, or women, and such analyses will be undertaken with the caveat that it is suggestive rather than causal.

In additional secondary analysis, at the hospital level, we will employ a regression discontinuity approach by comparing women who deliver in the hospital immediately prior to the intervention with women who deliver immediately post intervention to obtain an estimate of the causal effects of the intervention on the outcomes of interest in each hospital.

The analysis of the provider and facility surveys will be undertaken to estimate the extent of institutionalization and diffusion. We will estimate to what extent providers continue providing the service when they move to other institutions. We will examine these effects for staff at different levels of the provider workforce.

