### Randomization of hospitals

Because of the potential benefit of the intervention to all women, a cluster-randomized stepped wedge design was considered most appropriate for the study. Six hospitals were selected in each country to provide national geographic coverage, and were randomized into two groups of three. Facilities were matched by number of deliveries per year, and one was randomly selected from each pair to be assigned to Group 1 while the other was assigned to Group 2. Using Stata software, researchers at Harvard T.H. Chan School of Public Health generated a random number that was assigned to each hospital. The hospital with the higher random number in the pair was assigned to Group 2, while the hospital with the lower random number in the pair was assigned to Group 1. A full list of study facilities is available upon request. The study enrolment period for both groups will be 12 months in Tanzania and 18 months in Nepal and Sri Lanka. In Group 1, the baseline standard of care (SOC) period will be three months and the PPIUD intervention period will be nine months in Tanzania and fifteen months in Nepal and Sri Lanka. In Group 2, the baseline (SOC) period will be nine months and the PPIUD intervention period three months in Tanzania and nine months in Nepal and Sri Lanka. We can represent this design for each group as follows:

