**Table Taba:** 

Time (months)	1-3	4-9	10-12 (Tanzania) 10-18 (Nepal and Sri Lanka)
Group 1 (Hospitals 1-3)	O	X	X
Group 2 (Hospitals 4-6)	O	O	X
where X = PPIUD intervention and O = control (standard of care provided)			

Due to the randomized nature, the causal effect of the intervention on the outcomes of interest can be estimated. In months 4-9, a randomized contrast can be made that will be controlled for any secular trends in outcomes. In addition, before-after contrasts will be made within hospitals controlled for all time-invariant differences in event rates between hospitals. The reference population for the study will be all women in the catchment area delivering in each hospital within a period of 12 months from the start of the study in Tanzania and within a period of 18 months in Nepal and Sri Lanka.

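### The months 4-9 comparison, which the plan calls its strongest causal contrast, gives no effect estimate under the one model named, because no hospital changes status in those months

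*Protocol article*

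**What the plan says.** Only the protocol article is available.

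- **Design (Randomization of hospitals, and its table).** Each country has six hospitals. "Facilities were matched by number of deliveries per year, and one was randomly selected from each pair"; the hospital drawn starts first. "In Group 1, the baseline standard of care (SOC) period will be three months", and Group 2 stays on standard of care for nine months. The text adds: "In months 4-9, a randomized contrast can be made that will be controlled for any secular trends in outcomes". Before-after contrasts within hospitals are listed separately.
- **Model (Quantitative analyses).** The plan states that "individual-level conditional logistic regression models will be used, stratifying on hospital, and controlling for calendar time". The effect is carried by whether the woman's hospital was on standard of care or intervention when she delivered. The least adjusted version is described thus: "results will be reported adjusted only for hospital and calendar time". Fully adjusted results accompany it. Risk differences and risk ratios are to be derived from the odds ratios of this model.
- **Restriction (same section).** The months 4-9 subset is singled out: "Causal inference will be strongest when analysis is restricted to the subset of women enrolled during months 4-9 of the project". The only reservation that the plan attaches to this concerns sample size: "although power will likely be insufficient to detect effects of realistic sizes". No other model is named for this subset.

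**The concern.** A model stratified on hospital learns about the intervention only from hospitals observed in both conditions. The months 4-9 contrast is the opposite: it compares hospitals that differ in status and do not change it. The model and the restriction sit in the same section and cannot be combined. The stated caveat also points the wrong way. Low power suggests an estimate with a wide interval, whereas the named model gives no estimate. The contrast presented as the strongest causal evidence would then either go unreported or need an estimator chosen after the data are seen.

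**Working it through.** The plan gives no figure for this contrast, so there is none to reproduce. Its enrolment totals do reproduce (6 × 300 × 12 = 21,600; 6 × 300 × 18 = 32,400), but the main point does not depend on them.

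**1. Algebra.** Let hospital *j* have status *x_j*, constant over months 4-9, and *t_j* women with the outcome. Its conditional likelihood contribution is a ratio. The numerator is exp(β·x_j·t_j) times a calendar-time term. The denominator sums the same form over all sets of *t_j* women from that hospital. Every term carries exp(β·x_j·t_j), so it cancels and β disappears. Equivalently, status equals the sum of the three Group 1 hospital indicators. Status is constant in months 4-9 in all 18 hospitals, so pooling countries changes nothing.

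**2. Rank of the hospital-by-month design.**

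| Data used | Rank, hospital + month | Rank with status added | Columns |
|---|---|---|---|
| Months 1-12 | 17 | 18 | 18 |
| Months 1-18 | 23 | 24 | 24 |
| Months 4-9 | 11 | 11 | 12 |

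Without hospital strata, month plus status in months 4-9 has full rank (7 of 7), so a between-hospital estimator can identify the effect.

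**3. Simulated check.** On months 4-9 the conditional log-likelihood was -676.11 at status coefficients of -5, 0 and 5, and the fit returned 0 with a standard error of about 162. Over 12 months the same model gave 0.82 (standard error 0.16) for a true value of 0.8.

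**4. What a between-hospital analysis of months 4-9 alone offers.** Each hospital contributes 6 × 300 = 1,800 women. At the plan's upper ICC of 15%, the design effect is 1 + 1,799 × 0.15 = 270.9, and the effective size per group is 5,400 / 270.9 = 19.9. For uptake of 1% against 8%:

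- null standard error: √(2 × 0.045 × 0.955 / 19.9) = 0.0657
- alternative standard error: √((0.0099 + 0.0736) / 19.9) = 0.0647
- z = (0.07 − 1.96 × 0.0657) / 0.0647 = −0.91, so power is about 18%

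The same steps give about 45% at ICC 5% and 98% at ICC 1%. These use normal quantiles; a t reference on so few hospitals lowers them.

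**5. Permutation limits.** Three pairs: 2/2³ = 0.25. Nine pairs: 2/2⁹ = 0.004.

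**6. Gain from the months 1-3 baseline.** Inputs: the plan's rates (1% under standard of care, 8% under intervention), 900 women per hospital in months 1-3 and 1,800 in months 4-9. The between-period hospital correlation *c* is an assumption, because the article gives none. Worked at ICC 15% and c = 0.9:

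- v₁ = 0.08 × 0.92 = 0.0736; v₀ = 0.01 × 0.99 = 0.0099
- hospital-rate variance = ICC·v + (1 − ICC)·v/n: Group 1 months 4-9, 0.011075; Group 2 months 4-9, 0.001490; either group months 1-3, 0.001494
- covariances: c·ICC·√(v₀v₁) = 0.003644 (Group 1); c·ICC·v₀ = 0.001337 (Group 2)
- months 4-9 only: (0.011075 + 0.001490)/3 = 0.00419, standard error 6.5 points
- change score: (0.012565 + 2 × 0.001494 − 2 × 0.004981)/3 = 0.00186, standard error 4.3 points
- ANCOVA, common slope: (0.012565 − 0.004981²/(2 × 0.001494))/3 = 0.00142, standard error 3.8 points

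Variance reduction as ICC runs from 2% to 15%:

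| Assumed correlation | Change score | ANCOVA |
|---|---|---|
| 0.9 | 53.1-55.5% | 61.6-66.1% |
| 0.8 | 44.5-46.7% | 48.6-52.2% |
| 0.5 | 18.7-20.3% | 19.0-20.4% |
| 0.3 | 1.5-2.6% | 6.8-7.3% |

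The ANCOVA column treats the slope as known. With three pair differences, an intercept and a slope leave 3 − 2 = 1 degree of freedom; with nine they leave 7.

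**The case against.** The best defence is that the months 4-9 sentence is a remark about where inference is strongest and commits to no model. The design section treats that contrast as a between-hospital comparison, separate from the before-after contrasts, and an analysis plan that is not shown may name an estimator. This stands in part: the randomized contrast is sound, and the authors understood what kind of contrast it is. But the article does more than leave a detail open. It states one model, one adjustment set that includes hospital, and a restriction under which they yield no effect.

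Three stronger readings are tempting, and the document does not support them.

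- **That the trial's only randomization-protected analysis is lost.** The full-period model, adjusted for hospital and calendar time, also uses the randomized rollout and is estimable. It also already uses months 1-3 as each hospital's baseline.
- **That the plan would drop the strata and ignore clustering, with overconfident results.** No text says so. With 5,400 women per group and no clustering, power is about 100% for uptake of 1% against 8%, and about 99% for counselling of 1% against 2%. An expectation of insufficient power fits only an analysis that allows for clustering.
- **That baseline adjustment would save 59-80% of the variance.** That range comes from applying one average rate of 4.5% to both groups and both periods. The plan expects 1% or lower everywhere except under the intervention, and a near-zero baseline may predict later uptake poorly.

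**Conclusion.** The point holds for the months 4-9 subset. Under the only model named, the intervention odds ratio, and the risk ratio and risk difference derived from it, cannot be estimated there, whatever the sample size. The low-power caveat therefore misstates the problem. This follows from the design table alone and needs no assumption beyond adherence to the schedule and classification by month of delivery.

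The main full-period analysis is unaffected. The size of the benefit from using the baseline is uncertain: about 44-66% less variance at correlations of 0.8-0.9, about 20% at 0.5 and 1-7% at 0.3. It rests on the plan's uptake rates, ICC 2-15% and a correlation that the article does not give, before the cost of estimating a slope from few hospitals.

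**What to change.** In the Quantitative analyses section, keep the hospital-stratified model for the full period and name a different estimator for the randomized contrast:

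- Take each hospital's month 4-9 rate, by month of delivery. Adjust it by ANCOVA for the hospital's month 1-3 rate, and compare within the matched pairs. Use a permutation or small-sample t reference.
- State in advance how the slope is handled, given the few pairs.
- Report it beside the full-period model, with estimates and intervals by country. Add a test over the nine pooled pairs only if the plan's own between-country heterogeneity check supports pooling.
- Replace the power-only caveat with two statements: the stratified model does not apply in this subset, and three pairs cannot give a two-sided permutation p below 0.25.

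The cost is one paragraph and a little more analysis work, with no new data. Per-country power for this contrast will remain low.

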### Sample size

Following the cluster-randomized stepped-wedge design, power calculations were performed on a per country basis, assuming that 300 women are enrolled per hospital per month over a 12-month study enrolment period in Tanzania and an 18-month study enrolment period in Nepal and Sri Lanka, and followed for up to 18 months postpartum to ascertain study endpoints [13]. It is expected that the study will enrol 21,600 women in Tanzania and 32,400 women in Nepal and Sri Lanka.PPIUD Counselling – Assuming that at the study hospitals during the standard of care time periods, the PPIUD counselling rate will be 1% or lower, we will have 80% power or more to detect an increased counselling rate of 2% or greater, even with an ICC of 15% [14] or lower, assuming that at least 21,600 women are enrolled during the 12-18-month enrolment period.PPIUD Uptake – Assuming that at the study hospitals during the standard of care time periods, the PPIUD uptake rate will be 1% or lower, we will have 80% power or more to detect an increased PPIUD uptake rate of 8% or higher, even with an ICC of 15% or lower.PPIUD Expulsion Rate at 6 weeks – Assuming that the PPIUD uptake rate increased to 8% during the intervention periods at the study hospitals, there will be 80% power or greater if the PPIUD expulsion rate is assumed to be 20% before the intervention [15] and drops to 5% or less after the intervention, for an ICC of 5% or less, even with 20% loss to follow-up postpartum or less. These analyses apply only to the intervention periods at the six hospitals, and are based upon a one-sample test for clustered data.Modern contraceptive use at 6 weeks and 18 months – Assuming that modern contraceptive use at 6 weeks will be 55% in Sri Lanka [16] and that it will increase to 62% due to the availability of PPIUD during the intervention periods, there will be 80% power or more to detect this difference or anything greater, even if 20% of the participants enrolled during the antenatal period are lost to follow-up by the six week postpartum milestone and if the ICC is 15% or less. In Tanzania and Nepal, power is greater due to significantly lower modern contraceptive use at 6 weeks in the control group. Scenarios are similar for modern contraceptive use at 18 months.Proportion pregnant within 18 months of index pregnancy – Assuming that 24% of women who enrol during the control periods are pregnant again within 18 months [17], there will be 80% power or more to detect a decreased proportion pregnant by 18 months of 19.4% or less, even if 20% of the clients enrolled during the antenatal period are lost to follow-up by 18 months and if the ICC is 15% or less.

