
Thus, we conservatively expect excellent power within each of the 3 countries for all primary endpoints of this study, assuming 21,600 in Tanzania and 32,400 women in Nepal and Sri Lanka are enrolled across the study hospitals at a rate of 300/month. If between-country heterogeneity analysis indicates that the effect sizes between the countries appear to be comparable, we will pool the results across the three countries for substantially greater power.

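### Country-specific effects are tied to a significant interaction test and otherwise replaced by one pooled estimate, although the trial is powered by country and the test is weak for several endpoints

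*Protocol article*

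**What the plan says.** The Quantitative analyses section examines effect modification, by country and by other features, with likelihood ratio tests. It follows these by "reporting stratum-specific point and interval causal effect estimates for any statistically significant differences". For country it adds: "Should no effect modification by country be evident, we shall aggregate the data from the three countries and produce a single summary effect estimate". It also names the Q-test, I² and CV_B for differences between countries, without thresholds and without saying what will be shown.

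The Sample size section takes the country as its unit: "power calculations were performed on a per country basis", and "we conservatively expect excellent power within each of the 3 countries for all primary endpoints". It describes pooling as a further step, to be taken if the heterogeneity analysis suggests similar effect sizes. That criterion is looser than the significance test in the analysis section.

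No sentence says that country estimates will be withheld. No sentence commits to reporting them whatever the test shows.

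**The concern.** The rule lets a significance test on the trial's own data decide which estimates are presented. This has three consequences.

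- A non-significant result is read as grounds for a common effect. With three countries the test has 2 degrees of freedom and may have little power against differences that matter.
- The rule can set aside the country estimates for which the trial was sized. The article itself gives reasons why effects might differ: provider cadre, age limit, route into follow-up, length of enrolment and follow-up sampling all vary by country.
- Showing strata only where the difference is significant favours exaggerated differences.

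The Dissemination section aims the results at national societies, government officials and policy makers, who need the estimate and interval for their own country.

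**Working it through.** **Inputs from the article.** Recruitment: "300 women are enrolled per hospital per month". Six hospitals per country, three per group. Crossover: "In Group 1, the baseline standard of care (SOC) period will be three months" and "In Group 2, the baseline (SOC) period will be nine months". Design effects: counselling 1% to 2%, uptake 1% to 8%, modern contraceptive use 55% to 62%, pregnancy 24% to 19.4%. ICC 15%. Loss 20% for the last two.

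**Assumptions added here.** Two-sided alpha 0.05; Hussey-Hughes variance with monthly fixed effects and constant intra-hospital correlation; effects compared as risk differences; the stated rates applied to all three countries (the article gives 55% for Sri Lanka only).

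**1. Enrolment.** 300 × 6 × 12 = 21,600 and 300 × 6 × 18 = 32,400. This reproduces the plan's figures, the second one applying to Nepal and to Sri Lanka each.

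**2. Country standard errors.** For each hospital over T months with m women per month, V = τ²J + (σ²/m)I. The variance of the effect is the treatment element of (ΣX′V⁻¹X)⁻¹, where X holds the month effects and the intervention indicator. m is 300, or 240 after 20% loss. With p̄ the mean of the two rates, p̄(1−p̄) can be taken as the within-hospital variance (A) or as the total variance (B). The article does not say which, so both are shown.

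| Endpoint | SE in points, Tanzania / Nepal or Sri Lanka, A | Same, B | Per-country power, A |
|---|---|---|---|
| Counselling | 0.331 / 0.286 | 0.305 / 0.264 | 86% / 94% |
| Uptake | 0.564 / 0.488 | 0.520 / 0.450 | >99.9% / >99.9% |
| Modern contraceptive use | 1.498 / 1.298 | 1.381 / 1.197 | 99.7% / >99.9% |
| Pregnancy | 1.253 / 1.086 | 1.155 / 1.001 | 96% / 99% |

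The plan's claim of at least 80% power in each country holds under these assumptions.

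**3. Power of the interaction test.** With weights w = 1/SE², the noncentrality is λ = Σw(θ − θ̄)². If Tanzania has half the design effect d and the other two have all of it, λ = [w_T × 2w_N / (w_T + 2w_N)] × (d/2)². Power is P(χ²₂(λ) > 5.99).

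Pregnancy under A: w_T = 1/1.253² = 0.637 and 2w_N = 2/1.086² = 1.696. So λ = (0.637 × 1.696 / 2.333) × 2.3² = 2.45, and power is 27%.

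| Endpoint | λ, A / B | Power, A / B | Power if between-period correlation is 0.90 (assumed), A / B |
|---|---|---|---|
| Counselling | 1.66 / 1.96 | 19% / 22% | 7% / 7% |
| Pregnancy | 2.45 / 2.88 | 27% / 31% | 9% / 9% |
| Modern contraceptive use | 3.97 / 4.67 | 41% / 48% | 11% / 12% |
| Uptake | 28.0 / 33.0 | 99.9% / >99.9% | 46% / 53% |

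The 0.90 column is a sensitivity case only. The article gives no such value, and at 0.90 per-country power for pregnancy (A) falls to 36% / 46%, below the plan's claim.

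**4. Benchmark needing no variance model.** Per-country power of exactly 80% means d/SE = 1.96 + 0.84 = 2.80. With equal SEs and one country at half effect, λ = (2/3) × 1.40² = 1.31 and power is 16%. With one country at no effect, λ = (2/3) × 2.80² = 5.23 and power is 52%.

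**5. Consequence for the pooled figure.** Take true pregnancy reductions of 2.3 (Tanzania), 4.6 and 4.6 points, under A. The pooled value is (0.637 × 2.3 + 1.696 × 4.6) / 2.333 = 3.97. This is 3.97 / 2.3 = 1.73 times Tanzania's effect. The pooled SE is 1/√2.333 = 0.655, so a 95% interval centred there runs from 2.69 to 5.25 and excludes 2.3. The test misses the difference 73% of the time under A and 69% under B.

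**The case against.** The strongest counter-reading is that pooling is an addition and not a replacement. Power is set by country, pooling is introduced to gain more of it, and Q, I² and CV_B cannot be calculated without country estimates. A reader might infer from the rule that country results will be withheld or never published. The article does not say so, and it plans hospital-level estimates and release of the de-identified data. That inference is not supported. What remains is that the only stated condition for reporting estimates by stratum is significance, and the only stated product otherwise is a single summary.

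A reader might also infer that the test is weak throughout, the primary outcome of PPIUD uptake included. Under the article's ICC with constant correlation it is not: a halved uptake effect would be detected almost surely. Uptake becomes doubtful only under an added assumption (about 50% at a between-period correlation of 0.90) or for smaller differences (66% under A if Tanzania has three quarters of the effect).

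The article already says that subgroup analyses of providers, facilities and women are unpowered and only suggestive. That limits the harm from selective strata but does not remove the selection.

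Finally, a condensed article may leave table layouts to a fuller document. Here, however, the article states a rule, and the rule is what needs changing.

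**Conclusion.** The point holds as a badly fixed reporting rule that should be changed. Country and stratum estimates are conditional on a significant test, with one pooled estimate as the stated alternative, in a trial sized by country. A non-significant test would be weak evidence of a common effect for counselling, pregnancy and modern contraceptive use, where a halved effect in Tanzania is detected in fewer than half of trials. It would be reasonable evidence against a halving for uptake, if correlation within hospitals is constant over time.

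These sizes rest on the assumptions listed in the check. The planned likelihood ratio test works on the odds-ratio scale, so its power will differ somewhat. The 55% follow-up sample in Nepal and the satellite-clinic restriction in Sri Lanka and Tanzania were not modelled; they would lower power for the 9- and 18-month endpoints further.

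**What to change.** In Sample size and Quantitative analyses, state that the three country-specific estimates with confidence intervals will be reported for each endpoint whatever the interaction test shows. Report the country-stratified pooled estimate beside them, with Q, I² and CV_B as description and not as a gate. For other planned effect modifiers, report all stratum estimates with intervals for the interaction, keeping the existing caveat that these are suggestive.

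No extra women or models are needed. At planned enrolment the country 95% half-widths (1.96 × SE under A, Tanzania / Nepal or Sri Lanka) are 0.65 / 0.56 points for counselling, 1.1 / 1.0 for uptake, 2.9 / 2.5 for modern contraceptive use and 2.5 / 2.1 for pregnancy. The cost is a change of wording, one table or forest plot, and slightly longer reporting.
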